### 2.10 Concomitant care

Psychotropic medications (antidepressant, anxiolytic, hypnotic, antihistaminic, antipsychotic, anti-epileptic drugs and corticosteroids) will be permitted during the study, if clinically indicated. These treatments, class and dose, will be recorded in the electronic case report form, and analyses will be adjusted for these factors. As patients enrolled in the study are required to be in a stable post-therapy phase, minimal changes in drug dosage or regimen are expected during the study period, regardless of the randomization arm. This reduces the risk of bias due to intercurrent pharmacological modifications.

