If both patient and family caregiver agree, the family caregiver will provide an estimation of the patient's irritability and memory errors in daily life, by filling in the QMRP and BITe questionnaires (paper or digital version) at the same timepoints.

CBT sessions will not be recorded; however, the intervention fidelity and standardization will be ensured through regular supervision by a senior clinician, who will monitor the adherence to the manualized syllabus. All sessions will be delivered by the same trained onco-neuro-psychologist at all centers, ensuring consistency. In the rare event of absence, a senior clinician trained in CBT, neuropsychology and oncology will conduct the session, following the manualized syllabus. These measures provide structured oversight and preserve the intervention fidelity throughout the study.

In addition, baseline characteristics, compliance to the intervention (e.g., intervention adherence, session exposure, digital engagement) and other potential confounding parameters, such as psychotropic and anti-seizure drugs, corticosteroids, tumor laterality and eloquence, seizure frequency, and time since last treatment, will be collected/recorded in the electronic case report form to detect possible confounding effects.

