### 2.13 Data analysis

A statistical analysis plan will be drafted before database locking. For the for primary endpoint, all statistical analyses will be done using the intention-to-treat population and the evaluable population (i.e., patients with a FACT-Cog PCI score at baseline and M4).

Frequencies (N) and percentages (%) will be used to describe qualitative variables, and missing data reported. Percentages will be calculated after excluding missing data. Number of observations (N), median, minimum, maximum, mean, standard deviation, and interquartile range will be used to describe quantitative variables.

Baseline demographic and clinical characteristics, interventions and concomitant treatments will be described.

Questionnaire scores will be calculated according to established guidelines: FACT-Cog (Lange et al., 2016), QLQ-C30 and BN20 (EORTC manual), PRMQ (Guerdoux-Ninot et al., 2019), and neurocognitive and psychopathological tests (Gentile et al., 2003; Savard et al., 2005; Razavi et al., 1990; Beck et al., 1996; Bellaert et al., 2022; Nasreddine and Patel, 2016; Wechsler, 2011; Rieu et al., 2006; Bayard et al., 2023; Prevost et al., 2014; Spielberger, 1983; Guilmette et al., 2020). Scores will be reported and missing data rates recorded at all time points. Adherence rates will be estimated with their 95% confidence intervals.

The primary endpoint (FACT-Cog PCI score at M4) will be compared between arms with the Student's *t*-test or Wilcoxon/Mann-Whitney rank-sum test. An ANOVA or ANCOVA model will be used to adjust for potential confounders. A 5% significance threshold will be applied.

For the secondary endpoints:

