Second, the study does not include a measure of pre-morbid stress levels, although baseline stress significantly influences the psycho-oncological needs and coping trajectories in patients with LrGG (Ley et al., 2022). Without this information, interpreting inter-individual variability in outcomes may be more challenging.

Third, the digital neurocognitive tool displays robust psychometric properties in adults with other cancer types (Bray et al., 2017); however, its usability and applicability in patients with LrGG remain to be established. This study will carefully monitor adherence and patient feedback, providing important novel data to address this gap in a real-life cohort.

Fourth, subjective cognitive complaints are influenced by various sociodemographic variables, including age, sex, and socio-cultural level. As these variables will be collected, it will be crucial to include them as covariates in the analyses to take into account their potential confounding effects on the outcomes.

Fifth, the use of psychotropic drugs (e.g., antidepressant, anxiolytic, or antiepileptic drugs) may affect both cognitive performance and emotional wellbeing. As such treatments will not be standardized across participants and may differ between arms despite randomization, they may introduce a bias or variability in the results.

Sixth, all CBT sessions are delivered by the same therapist. This will ensure internal consistency, but may limit the generalizability of results to other clinicians or settings.

Lastly, the hybrid design of this study (CBT + digital tool) will not allow us to disentangle the effects of CBT and of the digital program because they are delivered concomitantly. Also, the hybrid design may lead to the unintentionally exclusion of individuals with limited digital literacy/access. Therefore, the intervention effectiveness could be partly explained by the participants' familiarity with digital technology and the proper functioning of the digital platform. This could limit the generalizability of the findings, especially to more vulnerable or socioeconomically disadvantaged patients.

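### Section 2.10 adjusts the analyses for drugs taken during the study without limiting this to baseline use, so the adjusted between-arm models may not estimate the effect of assignment to the program

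*Protocol article*

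**What the plan says.** Section 2.10 lists antidepressants, anxiolytics, hypnotics, antihistamines, antipsychotics, anti-epileptics and corticosteroids, which "will be permitted during the study, if clinically indicated". It continues: "These treatments, class and dose, will be recorded in the electronic case report form, and analyses will be adjusted for these factors". It then gives an expectation: "minimal changes in drug dosage or regimen are expected during the study period, regardless of the randomization arm". The section ends on the risk of bias from drug changes in the course of the study, so use after randomization is in view.

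Section 2.13 compares the FACT-Cog PCI score at M4 between arms with a t-test or rank-sum test. It adds: "An ANOVA or ANCOVA model will be used to adjust for potential confounders". The same pair of analyses is planned for the other questionnaire scores. Neither sentence restricts the covariates to baseline values.

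Section 2.12 names, among the items to be recorded, "compliance to the intervention (e.g., intervention adherence, session exposure, digital engagement) and other potential confounding parameters, such as psychotropic and anti-seizure drugs". These "will be collected/recorded in the electronic case report form to detect possible confounding effects".

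Two other places bear on the point. In section 2.7, concomitant treatments are recorded at the inclusion session, before the patient is randomized. In section 2.8.1, the CBT sessions are aimed at emotional regulation, fatigue and sleep, with insomnia components where needed.

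**The concern.** Randomization balances, in expectation, everything that precedes it. A variable that arises afterwards cannot confound the comparison of arms, but it can be changed by the arm. Use of sleep, anxiety or depression medication is a plausible example here, because the program treats the symptoms for which these drugs are given.

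If assignment changes drug use, adjusting for that use does two things. It removes any part of the program's effect that runs through drug use. It also compares patients who share a drug status but differ in underlying distress, because a program patient who still takes the drug is on average more distressed than a control patient who takes it. Distress itself lowers perceived cognition, so the arm coefficient shifts even when the drug has no effect of its own.

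At stake is the interpretation of the adjusted estimates, including the adjusted analysis of the primary endpoint. They could be reported as the effect of offering the program when they estimate something else.

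**Working it through.** **The plan's own figure.** Section 2.5 gives a difference of 6.5 (50 vs 56.5), SD 14, two-sided α 0.05 and 80% power; section 2.6 gives 2:1 allocation. The t-test calculation gives 55.26 control patients, rounded up to 56, plus 2 × 56 = 112 in the program arm: 168 evaluable, with power 80.5%. Then 168 / 0.90 = 186.7, so 187 enrolled. Both stated figures reproduce as an unadjusted two-sample comparison. The point changes neither.

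**Illustration of the adjustment.** The article gives no rate of drug use and no effect of the program on it. These inputs are therefore assumptions:
- allocation 2:1, total SD 14, true effect 6.5, higher PCI better (as in the sample-size figures);
- unmeasured distress worth −6 PCI points per SD;
- drug use logistic in distress (coefficient 1.2), 40% in the control arm;
- no effect of the drug itself on PCI.

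For a linear model with one added covariate,

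adjusted effect = unadjusted effect − (drug coefficient) × (use in program arm − use in control arm).

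In a large simulation of this model the drug coefficient is about −5.6 to −5.7. It is negative only because drug use marks distress. Putting in the numbers:

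| Use in program arm (control 40%) | Calculation | Adjusted effect | Change |
|---|---|---|---|
| 40% | 6.5 − (−5.6)(0) | 6.5 | 0% |
| 38% | 6.5 − (−5.6)(−0.02) | 6.4 | −2% |
| 35% | 6.5 − (−5.6)(−0.05) | 6.2 | −4% |
| 26% | 6.5 − (−5.7)(−0.14) | 5.7 | −12% |
| 56% | 6.5 − (−5.6)(+0.16) | 7.4 | +14% |

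The bias can go either way. With a true effect of 0 and use lowered to 26%, the adjusted estimate is −0.8. The unadjusted estimate stays at the true value in every row.

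**Sensitivity to the assumed model.** A second set of assumptions keeps 40% use in control and a total effect of 6.5. It lets the drug itself cost 0 or 5 PCI points. Distress is either absent or worth 7 points per SD and correlated 0.5 with drug use.

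| Fall in use (percentage points) | Adjusted effect | Power at 56/112, SD 14 |
|---|---|---|
| 0 | 6.5 | 81% |
| 5 | 6.0 to 6.2 | 74 to 78% |
| 10 | 5.4 to 6.0 | 66 to 75% |
| 20 | 4.3 to 5.5 | 47 to 67% |

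The power column uses the normal approximation and treats the shifted effect as the true one at an unchanged SD. It only translates the shift into familiar terms.

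**Compliance.** Table 1 marks CBT and BrainHQ as given to the experimental group only, so program compliance is defined only in that arm and nearly duplicates the arm indicator. Section 2.12 places it beside the confounders through the word other. Section 2.13 then speaks of adjusting for potential confounders. The link between the two is an inference.

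**The case against.** Four things can be said for the plan.

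First, the unadjusted test of the primary endpoint stands in section 2.13, directly before the sentence on ANOVA/ANCOVA, and the sample size matches it. This stands in full. A reader might infer that the randomized comparison as a whole is broken; the documents do not support that, since only the adjusted models are exposed.

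Second, section 2.10 expects little drug change in either arm, and entry allows psychotropic drugs only at stable doses. This stands as to size: under that expectation the shift is about 0 to 5% in the first model. But it is an expectation and not a rule. If it holds, baseline values serve as well as on-study values; if it fails, on-study adjustment biases the result. Nothing in the article suggests that the program would change anti-epileptic or corticosteroid use, so the point is narrower than the drug list.

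Third, the exact covariates can be settled in the SAP, and a model using class and dose at inclusion would satisfy section 2.10. This stands in part. The article does not fix the time point, but its sentence attaches to treatment permitted during the study, and an SAP that follows it literally would take the on-study values.

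Fourth, no adjustment for compliance is stated. Section 2.12 says these items are recorded to detect confounding, and adherence has its own secondary endpoint with confidence intervals. This stands. A reader might infer that the plan enters training hours in the primary model. If benefit were proportional to hours, that would take the arm coefficient from about 6.4 to about 0. The documents commit to no such model, so that figure does not describe the plan.

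Finally, the Discussion says of these drugs: "As such treatments will not be standardized across participants and may differ between arms despite randomization". A reader might take this as an admission that the program alters drug use. It describes imbalance from treatment that is not standardized and says nothing of cause.

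**Conclusion.** The point holds for the adjusted between-arm models. As written, section 2.10 calls for adjustment for drug use that may itself result from assignment, and section 2.13 does not confine covariates to baseline.

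The conclusion rests on one assumption that the article makes plausible but does not quantify: that a program aimed at distress, sleep and fatigue changes the use of at least some of these drugs. With no such change there is no bias. If drug change is as small as section 2.10 expects, the loss is modest: a 6.5-point effect becomes 6.2 to 6.5 in the first model, and 6.0 to 6.2 for a 5-point fall in the second. Larger changes matter more. All these figures are illustrative. This is a correction to make before the SAP is final; it does not put the unadjusted primary result in doubt.

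The grouping of compliance with confounders is a secondary matter of wording.

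**What to change.** In sections 2.10 and 2.13, state that covariates in all between-arm models are limited to values measured before randomization, for example drug class and dose at inclusion, baseline PCI and the stratification factors. The age, sex and socio-cultural variables named in the Discussion fit this rule. Report on-study changes in these drugs by arm descriptively.

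In section 2.12, take compliance out of the list of potential confounders and keep it for the adherence endpoint or a separate adherence analysis.

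The cost is wording only. Concomitant treatments are already recorded at inclusion, so no new data are needed, and 168 evaluable and 187 enrolled are unchanged.

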### 2.11 Safety

In this study, potential adverse events are expected to be mild, transient, and non-serious. Some participants may report temporary visual fatigue or slight headache related to the use of digital tools, including telehealth consultations and/or the digital cognitive rehabilitation program. These events are expected to resolve spontaneously and have no long-term consequence. All adverse events will be reported through the appropriate health vigilance systems in compliance with the current regulations. The investigator will inform the study sponsor (Montpellier Cancer Institute, France) about all new safety data that could influence the study benefit-risk assessment or will require updates to study documents. All patient safety concerns identified during the study period must be reported to the sponsor without delay.

### 2.12 Data collection

Patients will have access to a dedicated digital application (“*My trial Patient*”, Hoppen) to complete self-rated questionnaires (thus excluding clinician-rated neurocognitive assessments). Upon inclusion, they will receive a user guide and/or a trained staff member will assist them in accessing and using the application to ensure independent and accurate questionnaire completion. Patients will receive SMS reminders about the scheduled questionnaire completion dates. Patients who do not like to use digital applications will be able to complete the questionnaires in paper format.

Some assessments (i.e., BDI-II and STAI-Y questionnaires) will be provided in paper format by default with the material for specific neuropsychological tests (i.e., Visuospatial/Executive subtest of the MoCA, Symbol Search and Coding subtests of the WAIS-IV, and Trail Making Tests). Participants will be asked not to open the documents before the consultation time.

Remote testing procedures will be standardized. The onco-neuro-psychologist will administer all neuropsychological tests remotely via a telehealth platform. Each assessment will last between 1 and 1.5 h. Tests will always be administered in the same order, following strict standardized instructions, as specified in the manual of each cognitive test used (see references for each test). For paper-based tests (i.e., the Visuospatial/Executive subtest of the MoCA, Symbol Search and Coding subtests of the WAIS-IV, and Trail Making Tests), patients will complete the exercises at home under direct remote supervision by the onco-neuro-psychologist. Upon completion of each paper-and-pencil test, patients will show their work on screen, and the onco-neuro-psychologist will take a screenshot for record purposes. Patients are also instructed to return the completed tests by post to the study coordinating center using the provided pre-stamped and pre-addressed envelopes. All assessments will be conducted in accordance with the best practices in neuro-psychology and the standardized administration procedures specific for each test.

The patient engagement with the Brain HQ digital application will be monitored through automated usage metrics. Patients will not be constrained or directly supervised in their use; however, the onco-neuro-psychologist can address adherence issues during the telehealth CBT sessions if needed.

If both patient and family caregiver agree, the family caregiver will provide an estimation of the patient's irritability and memory errors in daily life, by filling in the QMRP and BITe questionnaires (paper or digital version) at the same timepoints.

CBT sessions will not be recorded; however, the intervention fidelity and standardization will be ensured through regular supervision by a senior clinician, who will monitor the adherence to the manualized syllabus. All sessions will be delivered by the same trained onco-neuro-psychologist at all centers, ensuring consistency. In the rare event of absence, a senior clinician trained in CBT, neuropsychology and oncology will conduct the session, following the manualized syllabus. These measures provide structured oversight and preserve the intervention fidelity throughout the study.

In addition, baseline characteristics, compliance to the intervention (e.g., intervention adherence, session exposure, digital engagement) and other potential confounding parameters, such as psychotropic and anti-seizure drugs, corticosteroids, tumor laterality and eloquence, seizure frequency, and time since last treatment, will be collected/recorded in the electronic case report form to detect possible confounding effects.

### 2.13 Data analysis

A statistical analysis plan will be drafted before database locking. For the for primary endpoint, all statistical analyses will be done using the intention-to-treat population and the evaluable population (i.e., patients with a FACT-Cog PCI score at baseline and M4).

Frequencies (N) and percentages (%) will be used to describe qualitative variables, and missing data reported. Percentages will be calculated after excluding missing data. Number of observations (N), median, minimum, maximum, mean, standard deviation, and interquartile range will be used to describe quantitative variables.

Baseline demographic and clinical characteristics, interventions and concomitant treatments will be described.

Questionnaire scores will be calculated according to established guidelines: FACT-Cog (Lange et al., 2016), QLQ-C30 and BN20 (EORTC manual), PRMQ (Guerdoux-Ninot et al., 2019), and neurocognitive and psychopathological tests (Gentile et al., 2003; Savard et al., 2005; Razavi et al., 1990; Beck et al., 1996; Bellaert et al., 2022; Nasreddine and Patel, 2016; Wechsler, 2011; Rieu et al., 2006; Bayard et al., 2023; Prevost et al., 2014; Spielberger, 1983; Guilmette et al., 2020). Scores will be reported and missing data rates recorded at all time points. Adherence rates will be estimated with their 95% confidence intervals.

The primary endpoint (FACT-Cog PCI score at M4) will be compared between arms with the Student's *t*-test or Wilcoxon/Mann-Whitney rank-sum test. An ANOVA or ANCOVA model will be used to adjust for potential confounders. A 5% significance threshold will be applied.

For the secondary endpoints:

- the FACT-Cog PCI scores will be compared between arms and time points using a similar method. A 5% significance threshold will be applied with adjustments for multiple comparisons to control the alpha risk using the Benjamini–Hochberg method (Benjamini and Hochberg, 1995). All exploratory analyses will be performed without adjustment.- Partial correlations between the FACT-Cog or PRMQ subscale score and key cognitive domains will be evaluated using Spearman or Kendall Tau correlation coefficients, adjusted for distress (HADS) and fatigue (MFI-20, ISI). Each neuropsychological threshold will be defined according to the test guideline and taking into account many variables, such as age, sex and/or socio-cultural level.- Other questionnaire scores will be compared between arms with the Student's *t*-test or Wilcoxon/Mann-Whitney rank-sum test. An ANOVA or ANCOVA model will be used to adjust for potential confounders.

Within each arm, score differences (HADS, PRMQ, BDI-II, STAI-Y, BITe, MFI-20, ISI, QLQ-C30, and BN20) between baseline and the subsequent timepoints will be assessed using the paired Student's *t* or Wilcoxon signed-rank test.

First, the mean score change over time will be graphically represented using the LOcally Estimated Scatterplot Smoothing method (LOESS).

Then, Linear Mixed Models (LMMs) may be used to model the score changes over time in function of the group. These LMMs will include random intercepts and slopes, assuming a linear trajectory over time. If necessary, more flexible LMMs (e.g., spline-based models) may be considered.

Although the open-label design may expose the study to attention and expectancy biases, particularly regarding self-reported outcomes, the data analysts involved in the primary outcome analysis will remain blinded to group allocation.

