### 2.3 Endpoint measures

The primary endpoint is the perceived cognitive impairment, assessed using the FACT-Cog PCI score (Lange et al., 2016) at M4. The self-report FACT-Cog questionnaire is used to assess subjective cognitive complaints and has been validated in patients with cancer. It also evaluates the cognitive impairment effect on HRQoL. It has a good internal consistency reliability (Cronbach's alpha between 0.74 and 0.91) and good convergent validity (significant correlations with the scores of scales assessing anxiety and depression).

Secondary endpoint measures will include:

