### 2.6 Randomization

Patients will be randomized in a 2:1 ratio (intervention: control) using a random block randomization method. This approach will maximize the number of patients who can benefit from the FREEDOME program. Stratification factors include:

Number of treatment lines (chemotherapy or radiotherapy, 0 vs. 1–2 vs. > 2);Baseline FACT-Cog PCI score (cognitive complaints) and HADS (distress) score (PCI score ≤ 47 and/or HADS score ≥13/42 vs. PCI score >47 and HADS score <13/42);Tumor histological grade (grade 2 vs. 3).

Investigators will register patients using the online electronic case report form (Ennov Clinical^®^).

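### The primary analysis lists a t-test or rank-sum test and then an ANOVA/ANCOVA without saying which decides, and does not name baseline PCI or the stratification factors as covariates

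*Protocol article*

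**What the plan says.** Section 2.3 defines the endpoint: "The primary endpoint is the perceived cognitive impairment, assessed using the FACT-Cog PCI score" at M4. It is the level at M4, not the change from baseline.

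Section 2.13 gives the analysis in three steps. First: "The primary endpoint (FACT-Cog PCI score at M4) will be compared between arms with the Student's *t*-test or Wilcoxon/Mann-Whitney rank-sum test". Next: "An ANOVA or ANCOVA model will be used to adjust for potential confounders". Then a single 5% significance threshold. No rule selects between the t-test and the rank-sum test, and no sentence says whether the two-sample test or the model is the deciding analysis.

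Section 2.6 lists three stratification factors: number of treatment lines (three levels), tumour grade (two levels), and a two-level composite built from "Baseline FACT-Cog PCI score (cognitive complaints) and HADS (distress) score", with cut-offs of 47 for PCI and 13 for HADS.

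Covariates are mentioned elsewhere. Section 2.10 says of psychotropic treatments recorded during the study that "analyses will be adjusted for these factors". The Discussion says of age, sex and socio-cultural level that "it will be crucial to include them as covariates in the analyses". Section 2.12 lists further items to be recorded as possible confounders, such as tumour laterality, seizure frequency and time since last treatment. None of these places names baseline PCI or the stratification factors as covariates.

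**The concern.** Two things are at stake.

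The first is which result counts. The t-test and ANCOVA both estimate a difference in means, one without and one with covariates. The rank-sum test addresses whether scores in one arm tend to exceed those in the other. With all of them listed under one 5% threshold and none ranked, the conclusion can depend on which is reported. The trial is open-label and has been recruiting since June 2024 (section 2.1), and the analysis plan is only promised before database lock, so the choice could be made late.

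The second is precision. Baseline PCI is the same instrument as the outcome and is likely to be among its strongest predictors. It is already available: the evaluable population in section 2.13 requires it. An analysis that omits it, and omits the factors used in the allocation, forgoes precision that costs nothing to obtain.

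**Working it through.** **Inputs.** From section 2.5: difference 6.5 points (50 versus 56.5), SD 14, two-sided alpha 0.05, power 80%, 168 evaluable, 10% attrition, 187 enrolled. From section 2.6: allocation 2:1, so 112 versus 56. The baseline-to-M4 correlation r is not in the documents; it is assumed and varied from 0.3 to 0.7.

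**Step 1: reproduce the plan's figure.** By the normal approximation, control-arm n = (1.96 + 0.842)² × 14² × (1 + 1/2) / 6.5² = 54.6, rounded up to 55, or 165 in total. With the noncentral t distribution, 55/110 gives power 0.798 and 56/112 gives 0.805, so 168 is the smallest 2:1 total that reaches 80% with an unadjusted t-test. Then 168 / 0.90 = 186.7, rounded up to 187. Both stated figures reproduce. A rank-sum test on normal data (relative efficiency 0.955) would have power of about 0.79 at the same size.

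**Step 2: precision with baseline PCI in the model.** The residual SD is 14 × √(1 − r²). The standard error is that SD × √(1/56 + 1/112) = SD × 0.1637, and the 95% half-width is about 1.97 × the standard error. Power is from the noncentral t.

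| r (assumed) | Residual SD | Power at 112/56 | 95% CI half-width (points) |
|---|---|---|---|
| unadjusted | 14.0 | 0.805 | 4.5 |
| 0.3 | 13.4 | 0.84 | 4.3 |
| 0.4 | 12.8 | 0.87 | 4.1 |
| 0.5 | 12.1 | 0.90 | 3.9 |
| 0.6 | 11.2 | 0.94 | 3.6 |
| 0.7 | 10.0 | 0.98 | 3.2 |

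Adding the stratification factors as well costs few degrees of freedom. With an intercept, arm, baseline PCI, treatment lines (2), the composite (1) and grade (1), the model has 7 parameters. It leaves 168 − 7 = 161 residual degrees of freedom, against 166 for the t-test.

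**Step 3: what an open choice can cost.** This was a null simulation with 8,000 runs per setting, 112 versus 56, normal data and two-sided 5% tests.

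| r (assumed) | t-test alone | Better of t-test and rank-sum | Best of t-test, rank-sum and ANCOVA |
|---|---|---|---|
| 0.3 | 4.6% | 5.5% | 6.8% |
| 0.5 | 5.6% | 6.7% | 8.7% |
| 0.7 | 5.2% | 6.0% | 9.4% |

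The simulation standard error is about √(0.05 × 0.95 / 8000) = 0.24 percentage points. The figures describe picking the smallest p-value. That is the worst use of an open list, and the protocol does not say it will be done.

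**Step 4: effect of ignoring the strata.** If allocation were stratified on a median split of PCI, the unadjusted t-test would reject under the null in about 4.4%, 3.5% and 1.6% of trials at r = 0.3, 0.5 and 0.7. It would be conservative. The trial's stratum mixes PCI with HADS and is less closely tied to PCI, so the effect here would be smaller.

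**The case against.** The strongest reply is that section 2.13 does plan an adjusted model, without condition and in the same paragraph as the two-sample test, and that a condensed article may leave the covariate list and the rule for choosing a test to the analysis plan. Much of this stands. A missing covariate list alone would be no finding. What remains is that the text fixes the primary analysis as a set of alternatives under one threshold. It also names covariates in two places, yet leaves out baseline PCI and the factors used at randomisation.

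Several stronger readings are tempting but not supported:

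- A reader might infer that the primary comparison is unadjusted. The sample size fits that reading, but the ANOVA/ANCOVA sentence contradicts it. The deciding analysis is open, so power is lost only if the unadjusted test turns out to decide.
- A reader might infer that the trial is underpowered. It is not: 80% is met without adjustment. The gain in step 2 is extra, and it depends on an unknown r. Entry requires a cognitive complaint (section 2.4.1), which may narrow the baseline range and lower r.
- A reader might infer that baseline imbalance would bias the result. Chance imbalance under randomisation is not bias, and the unadjusted test is valid, if somewhat conservative.
- A reader might infer that analyst blinding is offered as a guard against post-hoc test choice, and fails because 2:1 group sizes reveal the arms. Section 2.13 says that "the data analysts involved in the primary outcome analysis will remain blinded to group allocation" in a sentence about attention and expectancy biases of the open-label design. It makes no claim about test choice.

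**Conclusion.** The point holds as a defect of specification with a cheap remedy, not as an error that invalidates the planned test. Section 2.13 does not say which of the listed analyses decides, and neither baseline PCI nor the stratification factors are named as covariates.

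If the unadjusted test decides, the power forgone runs from about 4 percentage points (r = 0.3) through about 10 (r = 0.5) to about 17 (r = 0.7), above a planned 80% that is already met. These figures rest on an assumed r, a linear model and the plan's own SD and difference. The type I error of about 7–9% is illustrative: it assumes normal data and that the most favourable of three tests is reported.

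**What to change.** Name one primary analysis: an ANCOVA of M4 PCI on arm, continuous baseline PCI and the three stratification factors, reported as an adjusted mean difference with its 95% confidence interval. Label the t-test and the rank-sum test as sensitivity analyses.

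Do not adjust the primary model for drugs recorded after randomisation. The programme could itself change their use, so adjusting could remove part of its effect. The general statement in section 2.10 should be reconciled with this. Any further baseline covariates, such as age, sex and socio-cultural level, should be listed in advance or confined to secondary models.

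Settle this before any data are viewed by arm. The cost is wording in the protocol and analysis plan and five residual degrees of freedom. No new data are needed and the sample size need not change.
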